#### Clinical Scenarios requiring Guidance:

Positive margin: Patients should undergo re-excision per normal re-excision parameters

Positive sentinel lymph node (macrometastasis/micrometastasis): per Z11 if a patient has 1-2 positive sentinel LN, no further axillary dissection is required. If 3 or more sentinel LN are positive, axillary dissection should be considered unless the overall percentage of positive nodes is <20%. If a patient has a positive sentinel LN, whole breast radiation therapy should be delivered following surgical resection. In this scenario, this study will recommend conventional fractionation to the breast with an option to also treat the regional lymphatics as opposed to a hypofractionated 'short course' whole breast treatment alone. The rationale for this is that previous groups have identified a poorer cosmetic outcome when combining whole breast radiation therapy with pre-operative treatment. Therefore, we feel that it would be prudent to use conventional fractionated regimen when combining with pre-op radiation. A dose of 45 Gy in 1.8 Gy

fractions will be used for whole breast +/- a supraclavicular field for radiation therapy.

Isolated tumor cells in sentinel lymph node: no further axillary surgery. This specific scenario will be documented and it will be up to the discretion of the treating physician if whole breast radiation is required as above.

Microscopic ECE: if a node has microscopic ECE this will be treated as per bullet point 2 above. Macroscopic ECE should not be seen as these patients would be ineligible for treatment.

Patient refuses surgery: there may be instances where patients refuse surgical resection after receiving pre-op radiation. This is not the intent of the trial, however, the decision to undergo surgery is at the patient's discretion. In this scenario, the clinical team should document attempts to discuss with the patient. If ultimately the patient elects to not undergo surgery, the PI should be notified and a note to file will be placed in the patient's permanent medical record documenting attempts to discuss this with the patient and documenting the patient's refusal. This should also be sent to the UTSW radiation oncology study team.

#### **4.3.2 Medications**

##### Premedication

Analgesic premedication, such as Tylenol, and anti-anxiety medications such as Ativan, may be administered prior to therapy and as needed every 6 hours, to avoid patient discomfort.

##### Supportive Medicines

Consider Biafin during treatment period to reduce skin irritation. Consider analgesics such as Tylenol, Ibuprofen, or other NSAIDs for pain resulting from inflammation.

#### **4.4 Duration of Therapy**

Patients will receive one fraction of radiation.

#### **4.5 Duration of Follow Up**

Subjects will be followed for **5 years**. Subjects removed from treatment for unacceptable adverse events will be followed until resolution or stabilization of the adverse event. Patients will be followed 1, 3, 6, 12, 24, and 36 months after radiation. See [Section 5.4](#) Time and Events Table for follow-up visit windows.

#### **4.6 Removal of Subjects from Protocol Therapy**

Subjects will be removed from therapy when any of the criteria listed in [Section 5.5](#) apply. Notify the Principal Investigator, and document the reason for treatment discontinuation and the date of discontinuation. The subject should be followed-up per protocol.

#### **4.7 Subject Replacement**

If patient does not receive single fraction radiation therapy, that patient can be replaced in the study.

## 5.0 STUDY PROCEDURES

### 5.1 Screening/Baseline Procedures

Assessments performed exclusively to determine eligibility for this study will be done only after obtaining informed consent. Assessments performed for clinical indications (not exclusively to determine study eligibility) may be used for baseline values even if the studies were done before informed consent was obtained.

All screening procedures must be performed within 180 days prior to registration into the study unless otherwise stated. The screening procedures include:

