## 3.0 SUBJECT ELIGIBILITY

Eligibility waivers are not recommended; however, if warranted, prior approvals are required per Section 11.6.1. Subjects must meet all of the inclusion and exclusion criteria to be registered to the study. Study treatment may not begin until a subject is registered. Once registered, a subject is still required to meet all inclusion and exclusion criteria on the first day of treatment, prior to treatment.

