### 3.1 Inclusion Criteria

1. Invasive epithelial (ductal, medullary, lobular, papillary, mucinous (colloid), or tubular) histologies of the breast 3 cm or less (T1-T2cN0) in women who have not undergone surgery or neoadjuvant endocrine or chemotherapy for current breast cancer diagnosis
2. Tumor must not involve the overlying skin based on imaging evaluation and/or clinical exam
3. Age  $\geq$  18 years old and female
4. Greatest Tumor dimension is 3cm or less based on US. MRI measurements can be included only if performed BEFORE the biopsy
5. Tumor must be unifocal
6. The tumor must be visible on CT scan and/or preferably marked with clip(s) in tumor
7. Patients must undergo an MRI for work up to aid in tumor delineation and to rule out additional foci of disease. If additional foci of disease are present, they need to have a negative biopsy to proceed with treatment. If patient cannot have MRI, contrast enhanced digital mammography (CEDM) is allowed in place of MRI.
8. Clinically and radiographically node negative on ultrasound of the axilla or MRI
9. Estrogen receptor positive or Progesterone receptor positive and Her2neu negative
10. Ability to understand and the willingness to sign a written informed consent.
11. Women of child-bearing potential must agree to use adequate contraception (hormonal or barrier method of birth control) prior to the start of study and for the duration of radiation therapy. Should a woman become

pregnant or suspect she is pregnant while participating in this study, she should inform her treating physician immediately

A female of child-bearing potential is any woman (regardless of sexual orientation, having undergone a tubal ligation, or remaining celibate by choice) who meets the following criteria:

- Has not undergone a hysterectomy or bilateral oophorectomy; or
- Has not been naturally postmenopausal for at least 12 consecutive months (i.e., has had menses at any time in the preceding 12 consecutive months)

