### 3.2 Exclusion Criteria

1. Multi-centric disease
2. Prior RT to the involved breast
3. Tumor size >3cm
4. Uncontrolled intercurrent illness including, but not limited to, ongoing or active infection, symptomatic congestive heart failure, unstable angina pectoris, cardiac arrhythmia, or psychiatric illness/social situations that, in the opinion of the investigator, would limit compliance with study requirements
5. Patients who are pregnant or lactating due to the potential exposure to the fetus to radiation therapy and unknown effects of radiation therapy to lactating females
6. Patients unable to have an MRI or contrast enhanced digital mammography (CEDM)
7. Prior ipsilateral breast cancer
8. Tumor less than 5mm from the skin surface on clinical exam and/or radiographic imaging
9. Patients with active Lupus or scleroderma

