#### 5.1.13 *Pregnancy test (for women of childbearing potential)*

See section 3.1.11 for definition.

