## **5.2 Procedures During Treatment**

### **5.2.1 Baseline/Prior to Radiation Therapy**

- Breast Assessment/Examination
- Breast Imaging (see section 5.1.10 for details)
- Breast MRI or contrast enhanced digital mammography(CEDM) (see section 5.1.14 for details)
- History and Physical Exam (including Performance Status)
- Baseline adverse event assessment
- Baseline breast digital pictures
- Patient and Physician Cosmesis Forms
- Optional blood samples for correlative studies within 30 days prior to radiation
- Tumor sample from diagnostic biopsy
- Optional Tumor Sample within 30 days prior to radiation.
- Pregnancy Test (if applicable)

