| Performance Status                                | X               |                          |                                |                 |                                    |                                 |                                 |                                 |                                  |                                  |
| Pregnancy Test                                    | X               |                          |                                |                 |                                    |                                 |                                 |                                 |                                  |                                  |
| Baseline AE Evaluation                            | X               |                          |                                |                 |                                    |                                 |                                 |                                 |                                  |                                  |
| Toxicity/AE Evaluations (including DLT)           |                 |                          | X                              |                 |                                    | X                   | X                               | X                               | X                                | X                                |
| Breast Imaging (Mammogram/ US, and or Ultrasound) | X               |                          |                                |                 |                                    |                                 |                                 | X                               | X                                | X                                |
| Breast MRI                                        | X   |                          | X                  |                 |                                    |                                 |                                 |                                 |                                  |                                  |

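### The pregnancy test is timed only by the 180-day default counted back from registration, so no test supports the treatment-day eligibility check before the single fraction

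*Protocol*

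**What the plan says.** **Screening window.** Protocol section 5.1 states: "All screening procedures must be performed within 180 days prior to registration into the study unless otherwise stated". It also says that assessments done solely to determine eligibility come after consent, while clinically indicated assessments made before consent may serve as baseline values.

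**The test.** Section 5.1.13 lists it as a screening procedure, "Pregnancy test (for women of childbearing potential"), and adds only a pointer to the definition of child-bearing potential. Section 5.2.1 lists "Pregnancy Test (if applicable") among the procedures before radiation, without a number of days. The row "Pregnancy Test" in the section 5.4 table has a single mark in the pre-radiation column, with no footnote and no repeat.

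**The exclusion.** Section 3.2 excludes "Patients who are pregnant or lactating due to the potential exposure to the fetus to radiation therapy", and gives exposure to radiation as the reason. Section 3.0 says that, once registered, "a subject is still required to meet all inclusion and exclusion criteria on the first day of treatment, prior to treatment".

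**Other safeguards.** Inclusion item 11 asks this of participants who could become pregnant: "must agree to use adequate contraception (hormonal or barrier method of birth control) prior to the start of study and for the duration of radiation". A participant who suspects pregnancy is also to tell her physician at once. Section 5.5.7 lists pregnancy as a reason for removal, reported on the timelines of a serious adverse event.

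**The concern.** Section 3.0 sets a condition for the day of treatment, while section 5.1 times the only evidence for it from an earlier and unconnected date. A site can follow every scheduling rule and still reach the treatment day with a pregnancy result that says little about that day.

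The stake is the one that section 3.2 names, fetal exposure to radiation. Section 4.4 says: "Patients will receive one fraction of radiation". With a single fraction, a pregnancy discovered afterwards cannot lead to later fractions being withheld. The whole protection lies in what is known before the beam is switched on.

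**Working it through.** The protocol states no figure to reproduce. The check sets its timing rules side by side and adds the intervals they allow.

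**Step 1: which window governs the test.** The 180-day default applies unless another window is stated. The three places where one could be stated are:

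| Place | Timing given for the pregnancy test |
|---|---|
| Section 5.1.13 | None; refers to the definition of child-bearing potential |
| Section 5.2.1 | Before radiation; no number of days |
| Section 5.4 table | One mark, pre-radiation column; no footnote, no repeat |

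Sections 5.2.1 and 5.4 fix the order (test before radiation) but not the interval, so the default applies.

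**Step 2: permitted age of the result at irradiation.** Let S be the days from test to registration and G the days from registration to radiation.

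Age at irradiation = S + G, with S at most 180 (section 5.1) and G without a stated maximum.

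- If treatment falls on the day of registration (G = 0), the age can be up to 180 + 0 = 180 days.
- If G is assumed to be 30 days, purely for illustration, the age can be up to 180 + 30 = 210 days.
- For any other G, the limit is 180 + G. Section 3.0 requires only that registration come before treatment.

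**Step 3: comparison with other items before radiation.** Footnotes 3 and 8 of the section 5.4 table require the optional blood and optional tumor samples within 30 days before radiation. Even at G = 0, the age allowed for the pregnancy result is 180 / 30 = 6 times as long. Those two windows are also anchored to radiation, and the pregnancy test's window is not.

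**Step 4: whether the treatment-day check supplies a test.** Section 3.0 requires the criteria to hold that day but names no procedure for confirming them. The section 5.4 table has no treatment-day column; it passes from the pre-radiation column to the one covering the 14 days after radiation. No repeat test is scheduled.

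**Step 5: what else bears on the treatment day.** The contraception agreement and the duty to report a suspected pregnancy remain. Neither is a test. Because section 5.1 accepts clinically indicated results from before consent, a qualifying test can also predate the contraception agreement. The agreement would not reveal a pregnancy that began between the two.

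**The case against.** The strongest reply is that the exclusion does apply at irradiation, because section 3.0 says so. Contraception is required up to and through the fraction, a woman who suspects pregnancy must report it, and pregnancy is a reason for removal. All of this stands. A reader might infer that the exclusion is not enforced at irradiation, and the documents do not support that. What is missing is a timed test behind the requirement.

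A second reply is that 180 days is an outer limit. A test done only for eligibility must follow consent, so a result that old needs either a long gap between consent and registration or reuse of a clinically indicated test. This also stands, and it makes the extreme case less likely. Section 5.1 nevertheless permits both routes.

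A third is that the 30-day windows belong to optional correlative samples rather than safety checks. That is correct, and the comparison does not show what the right interval is. It shows that the protocol anchors other items to radiation and leaves this one unanchored.

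Two wider readings should be set aside:

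- **Before surgery.** A reader might infer that the exclusion also fails between radiation and surgery. Its stated reason is radiation exposure, which has ended by then, and no section makes it a condition for surgery.
- **Contraception.** A reader might see a contradiction in contraception being required only through the single fraction, or in hormonal methods being allowed in a receptor-positive population that then starts endocrine therapy. These provisions can all be followed as written. Choosing a contraception period or method would be a clinical rule, which this review does not propose.

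**Conclusion.** The point holds for the timing of the test. As written, a pregnancy result up to 180 days old at registration, and older by an uncapped interval at irradiation, satisfies the schedule and can be the only objective evidence for a condition that section 3.0 places on the treatment day.

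This rests on two readings: that section 5.1.13 falls under the section 5.1 default, and that an entry before radiation without a number of days does not count as a window stated otherwise. The protocol does not say what share of participants would be of child-bearing potential, so the number affected cannot be estimated; eligibility starts at age 18. The definition of dose-limiting toxicity and the escalation rule are untouched. The gap concerns participant and fetal safety, and it is cheap to close.

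**What to change.** Reconcile sections 3.0, 5.1, 5.1.13, 5.2.1 and 5.4. State in section 5.1.13, and repeat in a footnote to the pregnancy-test row of section 5.4, a window for the test counted back from the radiation fraction rather than from registration. Link that result to the treatment-day eligibility check in section 3.0. The sponsor should choose the interval.

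The test is already required, so the change is to its timing. The cost is a few lines of wording and an occasional repeat test when treatment is delayed.

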#### 5.1.1 *Informed Consent*

#### 5.1.2 *Medical history*

Complete medical and surgical history, breast and lymph node examination and palpable size of tumor. Any ongoing signs/symptoms present during Screening should be assessed and graded per CTCAE, and followed as per section 7

#### 5.1.3 *Demographics*

Age, gender, race, ethnicity

#### 5.1.4 *Review subject eligibility criteria*

#### 5.1.5 *Review previous and concomitant medications*

#### 5.1.6 *Physical exam including vital signs*

Vital signs (temperature, pulse, respirations, blood pressure)

#### 5.1.7 *Performance status*

Performance status evaluated prior to study entry according to Appendix I

#### 5.1.8 *Adverse event assessment*

Baseline adverse events will be assessed. See section 7 for Adverse Event monitoring and reporting.

#### 5.1.9 *Breast Assessment/Examination*

#### 5.1.10 *Breast Imaging*

Mammogram and Ultrasound of breast and axilla prior to treatment

#### 5.1.11 *Blood draw and tumor biopsy at baseline and surgical specimen for correlative studies*

Peripheral blood samples will be collected within 30 days prior to radiation therapy treatment, 4 weeks following completion of the radiation therapy delivery, and 4 weeks after surgery. Samples will be stored per human use and institutional protocols and guidelines. At the present time, we do not have funding for further analyses of these samples. However, we do anticipate receiving funding to undertake such correlative studies. UTSW has agreed to store and house blood and tissue samples.

We will also attempt to obtain tissue from the tumor biopsies per Section 5.4 of Time and Events table. The tumor samples from biopsies prior to radiation treatment and within 14 days after radiation treatment are optional. The tumor

sample collected at time of surgery is mandatory and will be collected for each patient. See [Section 9.0](#) for correlative study details.

#### 5.1.12 *Photographs*

Photographs of the patient's breasts should be taken prior to radiation therapy. The first photo should be a close-up encompassing only the breast to be treated at a 45 degree oblique angle with arms elevated over the patient's head. The second photo should be a straight frontal view of both breasts taken in either a standing or seated position with the patient's hands on her hips, excluding her face. Label each slide or photograph with the date and the patient case number. See section 6.2 for photo evaluation criteria.

#### 5.1.13 *Pregnancy test (for women of childbearing potential)*

See section 3.1.11 for definition.

#### 5.1.14 *Breast MRI*

Baseline Breast MRI will be required to determine eligibility, however if patient is unable to have an MRI, contrast enhanced digital mammography (CEDM) is allowed in place of the MRI. This is per standard of care for a patient with a new diagnosis. **An additional optional breast MRI is highly recommended and may be completed at least 4 weeks after radiation.**

The research being done with serial MRI scans is to determine whether they can help assess response in women receiving Gammapod, MR Linac, or Cyberknife therapy to monitor treatment changes prior to surgery. **MRI scans will be performed at two time points before and after radiotherapy to determine treatment response.** Each imaging exam will last approximately one hour. It is recommended but not mandatory. Breast MRI can be performed on either a 1.5T or 3.0 T scanner; it is preferred that all MRI exams for a given participant be performed using the same MRI field strength.

If possible, the MRI scanner make/model (e.g., GE, Siemens, Philips, Toshiba), breast coil, contrast agent, and image acquisition protocol should also remain consistent for each MRI exam a participant receives at UTSW. This is not mandatory but highly recommended as some patients may get MRI at outside facilities.

Prior to each MRI exam, the participant will be asked to complete or update a metal screening form. An intravenous catheter will be inserted in the participant's arm or hand prior to the start of imaging. The imaging exam will be performed with the participant lying on her stomach.

**The recommended but not mandatory image acquisition protocol** will include a localization scan, a T2-weighted imaging sequence, a diffusion-weighted imaging sequence, and a T1-weighted contrast-enhanced imaging series. For contrast-enhanced imaging, Gadavist will be administered intravenously at a dose of 0.1 mmol/kg body weight followed by a saline flush. Contrast injection will begin simultaneously with the start of data acquisition.

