#### MRI post processing

Subtraction series of all dynamic post contrast sequences will be obtained. Maximum Intensity Projection (MIP), and ADC maps of the Diffusion weighted series will be obtained. DWI difference will be computed between baseline and post radiation therapy.

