### **6.1.2 Methods for Pre-operative Evaluation of Measurable Disease**

All measurements should be taken and recorded in metric notation using a ruler or calipers. All baseline evaluations should be performed as closely as possible to the beginning of treatment and not more than Response Criteria on MRI. Response assessment to stereotactic radiotherapy will be performed using contrast-enhanced dynamic breast MRI (DCE-MRI) imaging.

Recommended MRI technique: (may not be possible for all MRI's as some may be done at outside facilities)

Recommended MRI studies will be performed with the patients lying prone in a scanner using a dedicated multi-channel breast array coil (MRI Devices Corporation, Pewaukee, WI). The breast MRI protocol is attached and will comprise pre-and post contrast dynamic 3-dimensional fast spoiled-gradient echo image sets, as well as diffusion weighted image series (DWI). Images will be obtained during and following rapid intravenous bolus infusion of gadolinium contrast at a rate of 3 mL/sec with a power injector (Spectris Solaris MR Injector; Medrad, Warrendale, PA) with delayed postcontrast 3-dimensional fast spoiled-gradient echo images with fat suppression in both axial and sagittal planes obtained.

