#### Imaging response assessment

i. The precontrast dynamic image set will be subtracted from the postcontrast sets, and time-intensity curves will be obtained from contrast-enhanced lesions with a hand-drawn region of interest (ROI) encompassing the lesion, with a

minimum ROI size of  $3 \times 3$  pixels. The time-intensity curve demonstrating maximal change will be selected as representative for a lesion to perform pharmacokinetic analysis as needed. Further same measurements will be performed from peritumoral stroma (within 2 cm of the tumor margins) to measure the radiation effect on stroma.

ii. *Volume changes*: Tumor enhancement volume (signal enhancement ratio) prior to and after therapy will be derived using dedicated software (DynaCAD, Philips) and post-therapy enhancement volume change (%) will be computed. In addition, percentage change in tumor size will be assessed using the following formula for ellipsoidal or spherical volume derived from mid-dynamic sequence subtraction series:

$$V (\text{cm}^3) = (4/3 \pi) \times \text{length}/2 \times \text{width}/2 \times \text{height}/2$$

iii. *Pharmacokinetic Analysis*: In the subgroup of patients who undergo baseline and follow up MRI imaging in our institution, A 3-parameter, 2-compartment general kinetic model will be used to derive PK parameters (Ktrans, kep, and ve). A Weimann arterial input function will be used as the population model. Parameters Ktrans (min), kep (min), and ve (unitless) will be computed from the change in signal intensity data, which is converted to gadolinium concentration pixel-by-pixel within a defined ROI. The mean values of these parameters will be compared pre-and post therapy.

iv. *Kinetic changes*: Model-independent analysis will be performed by directly measuring of the slopes of signal intensity wash-in and wash-out curves (maximum slope, sec), contrast enhancement ratio, and IAUC90.

v. *Diffusion Weighted Imaging when performed- changes* within the tumor, both DWI signal and ADC values will be measured and compared to pre-treatment values as applied.

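### The DWI, kinetic and enhancement-volume changes may be computed from MRI pairs taken on different scanners, where a scanner difference cannot be separated from radiation response

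*Protocol*

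**What the plan says.** Section 5.1.14 states that "Breast MRI can be performed on either a 1.5T or 3.0 T scanner" and that "it is preferred that all MRI exams for a given participant be performed using the same MRI field strength". It asks for consistent scanner model, coil, contrast agent and acquisition protocol for exams done at the institution, then adds: "This is not mandatory but highly recommended as some patients may get MRI at outside facilities". Section 6.1.2 repeats that the recommended technique "may not be possible for all MRI's as some may be done at outside facilities".

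The change measures are set out as follows:

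- MRI post processing (under 5.1.14): "DWI difference will be computed between baseline and post radiation therapy".
- Imaging response assessment (under 6.1.2), item ii: "post-therapy enhancement volume change (%) will be computed", together with a change in ellipsoid size.
- Item iii, pharmacokinetic parameters: "In the subgroup of patients who undergo baseline and follow up MRI imaging in our institution".
- Item iv: signal-intensity wash-in and wash-out slopes, contrast enhancement ratio and IAUC90.
- Item v, diffusion imaging where performed: "both DWI signal and ADC values will be measured and compared to pre-treatment values as applied".

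The MRI Analysis paragraph then relates the volume, kinetic and DWI parameters to pathologic response by logistic regression. It describes a univariate model for each imaging parameter and names no scanner or field-strength term.

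**The concern.** A within-patient change measures tissue response only if both scans measure on the same scale. Raw DWI signal is in arbitrary scanner units, so its difference across two scanners has no fixed meaning. Signal slopes, enhancement ratios and enhancement-based volumes depend on sequence, field strength and contrast agent. ADC is a derived quantity and is less exposed, but it is not immune. The protocol permits mismatched pairs and, outside the pharmacokinetic item, does not say how to handle them.

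At stake is the question the serial MRI is meant to answer: whether the scans help to assess response before surgery. Mismatch that is unrelated to response adds noise to the predictors and pulls the odds ratios towards 1. Mismatch that runs mainly in one direction also shifts the mean change and can look like a treatment effect.

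**Working it through.** The protocol gives no figure to reproduce. The finding rests on comparing the provisions.

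**Step 1. Which measures are limited to comparable pairs?**

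| Measure | Scanner-dependent? | Limit stated |
|---|---|---|
| Enhancement volume change (ii) | Yes, based on signal enhancement | None |
| Ellipsoid size change (ii) | Least, three diameters | None, and little need |
| Pharmacokinetic parameters (iii) | Yes, though signal is converted to gadolinium concentration | Both scans in-house |
| Slopes, enhancement ratio, IAUC90 (iv) | Yes, taken from signal without a kinetic model | None |
| DWI signal (v) | Most, arbitrary units | Only where DWI was performed |
| ADC (v) | Less | Only where DWI was performed |
| DWI difference (post processing) | Depends on whether signal or ADC is meant, which is not stated | None |

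Items iii and iv use the same dynamic series. Item iv skips the conversion to concentration, so it is at least as exposed as item iii, yet only item iii is limited. That limit is by institution, so it does not guarantee equal field strength either.

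**Step 2. How large could the effect be?** Every input here is an assumption, because the documents give none: mismatched share f = 0.2 to 0.5; scanner shift s = 5 to 15 percentage points of ADC change; between-patient SD of the true change = 15 points.

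*Shift in one direction.* Bias in the mean change = f × s: from 0.2 × 5 = 1.0 to 0.5 × 15 = 7.5 points.

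*Random shift with SD s.* The correlation with pathology is multiplied by √(15² / (15² + f·s²)). Using matched pairs only removes this attenuation but keeps a fraction 1 − f of the pairs. The association signal, correlation × √(number of pairs), is then multiplied by √(1 − f).

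| f | s | All pairs | Matched pairs only |
|---|---|---|---|
| 0.2 | 5 | √(225/230) = 0.989 | √0.8 = 0.894 |
| 0.2 | 15 | √(225/270) = 0.913 | 0.894 |
| 0.5 | 5 | √(225/237.5) = 0.973 | √0.5 = 0.707 |
| 0.5 | 15 | √(225/337.5) = 0.816 | 0.707 |

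These factors are for correlations. A linear slope shrinks by the square, 225/230 = 0.978 to 225/337.5 = 0.667, and a log odds ratio behaves only approximately like that.

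*Fixed shift in some patients only.* With the shift s now in SDs of the true change, and mismatch unrelated to response, the linear slope is multiplied by 1/(1 + f(1 − f)s²). This gives 1/1.0225 = 0.98 at f = 0.1, s = 0.5, and 1/1.25 = 0.80 at f = 0.5, s = 1.

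**Step 3. Reading.** At all four corners of the random-shift range, keeping every pair preserves more signal for detecting an association than dropping the mismatched ones. Matched pairs give the estimate that is free of scanner effect. The two analyses answer different needs, so both are wanted.

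**The case against.** The strongest reply is that the protocol permits mismatch but does not show that it occurs. The same field strength is preferred, consistent equipment is strongly recommended, and no sentence says that mismatched pairs must be pooled. A statistical analysis plan, not shown here, could select pairs or adjust for scanner. The second MRI is optional, and change on MRI is neither the primary endpoint nor a listed secondary one. The listed radiomics objective uses pre-treatment MRI.

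Most of this stands, and it limits the point. It does not remove it, because the protocol itself fixes the analysis set item by item and does so for one scanner-dependent measure only.

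A reader might infer three stronger claims that the documents do not support:

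- **The error runs in the direction of a treatment effect.** This needs baseline scans to come mainly from outside and second scans from the institution. Section 5.1 allows clinically indicated scans obtained before consent to serve as baseline, so this is possible, but the protocol does not give the split. A shift common to all patients would leave the logistic slope unbiased.
- **The sponsor recognised the problem and solved it once.** Item iii gives no reason for its limit, and the need to convert signal to gadolinium concentration could explain it.
- **All mismatched pairs should be excluded.** Under the assumed random shifts, exclusion costs more power than it saves, in a trial capped at 60 patients.

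**Conclusion.** The point holds in a limited form. Sections 5.1.14 and 6.1.2 allow the two MRIs of one patient to differ in field strength, scanner, contrast agent and acquisition protocol. All the scanner-dependent changes except the pharmacokinetic ones may be computed from such pairs and entered in the logistic models. In those pairs, scanner difference and radiation response cannot be separated.

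The number of affected pairs and the size and direction of the error are unknown. The 1.0 to 7.5 points of mean bias and the correlation factors of 0.99 to 0.82 rest wholly on assumed inputs. The case is firmest for raw DWI signal, whose units are arbitrary, so no bound can be given. It is weaker for ADC and weakest for ellipsoid size. Dose escalation and the DLT/MTD endpoint are unaffected. The change is worth making because it is cheap and the scan details may be hard to recover later.

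**What to change.** In Sections 5.1.14 and 6.1.2:

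1. Replace the raw DWI-signal difference by ADC change, or by signal normalised to a reference tissue, and say which one the post-processing paragraph means.
2. Record field strength, scanner, sequence and b-values, and contrast agent on the CRF for each MRI, including outside scans.
3. For ADC, kinetic slopes, enhancement ratio and enhancement-volume change, report the analysis in pairs with the same field strength and acquisition protocol beside the all-pairs analysis. The alternative is to adjust for a mismatch indicator. That adds a term to the univariate models and removes only an average shift, not random scanner variation.
4. Keep mismatched pairs in the ellipsoid size analysis throughout.

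The matching rule in item 3 is new: the in-house limit of the pharmacokinetic item would not by itself secure equal field strength. The cost is protocol wording, a few CRF fields and one extra analysis. The downside is fewer pairs and lower precision in the matched-pair results. No additional scans are needed and no patient is excluded from the trial.
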